### Consent

Written active consent from both a parent/guardian and the participant was required by the Ethics Committee's to access data for the longitudinal component of the research study until the participants reached the age of 20 (intervention and control arms). The consent specifically included permission for the research team to access data relating to pregnancy from hospital administrative records and abortion clinics. In a bid to maximise participation rates, four additional research staff were recruited to support School Health Nurses in their recruitment efforts. Despite best practice recruitment procedures, approved incentives and significant time and resources, the participation rates at the student level remained relatively low (Refer to Table 1). This is considered further in the discussion section of this paper.

**Table 1 T1:** Participation rates at the Individual level

Study Arm	Students approached	Consented & participated	Participation rate	Mean participants per cluster	Participant range per cluster
Intervention	2177	1267	58%	47	3-166
Non-intervention	3510	1567	45%	54	13-163

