### Sample Size Calculation

The required sample size was calculated using a method that took into account the intra-cluster correlation coefficient, the anticipated effect size, the desired power, and the expected number of events. Utilising methods described by Schoenfeld and Richter [43] to calculate the required sample size, we assumed an average of 50 participants per school, a conservative intra class correlation (ICC) of 0.02 (equating to a design effect of 2), and sought to detect a 25% magnitude of difference in pregnancy rate at the 5% significance level with 80% power. Power calculations were made with a one sided test in mind as we were seeking to see a reduction in the number of pregnancies in the intervention compared to the non intervention group (a result of no difference or indeed an increase in pregnancy rate would be interpreted as the VIP Program failing in its primary outcome). The expected birth rate, abortion rate and pregnancy rate in the control group were estimated from WA Department of Health figures specific to the age and postcode of residence that matched the study population (6% expected to have live birth, 10.8% abortion, and thus 16.8% known pregnancy). The minimum required number of participants was estimated to be around 1,300 per study arm. It was expected that over the follow-up period the magnitude of clustering effects would decline as the students leave school and the prevalence of risk behaviours such as unprotected sexual activity become less influenced by school peers. Loss to follow-up was not considered to be a significant factor in this research design as the primary outcome measures are being obtained via the Western Australian Data Linkage System (WADLS). Any participant who has a birth or an induced abortion in a hospital or day surgery facility within the state of Western Australia should be tracked through the WADLS. Participants having a birth or abortion outside of Western Australia between the age of recruitment and the time they turn 20 would not be identified by the record linkage system; however it is assumed there would be no difference in rate of migration out of the State between the trial arms.

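### The stated minimum of about 1,300 per arm does not follow from the plan's own inputs, which need about 1,715 to 2,060; at 1,300 the one-sided power is about 63-70%, not 80%

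*Protocol article*

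**What the plan says.** All inputs and the result stand in the protocol article, under Sample Size Calculation.

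- Clustering: the authors assumed "an average of 50 participants per school, a conservative intra class correlation (ICC) of 0.02 (equating to a design effect of 2").
- Target: they "sought to detect a 25% magnitude of difference in pregnancy rate at the 5% significance level with 80% power".
- Sidedness: "Power calculations were made with a one sided test in mind".
- Control rate: 6% live births plus 10.8% abortions, giving 16.8% known pregnancies. These are described as control-group expectations.
- Method: a cited time-to-event sample size method. No allowance is made for loss to follow-up.
- Result: "The minimum required number of participants was estimated to be around 1,300 per study arm".

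After the result, the section adds that clustering was expected to weaken as students left school, without a number. It also says that no difference, or an increase, would be taken to mean that the program had failed on its primary outcome.

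The Abstract describes even randomisation. Table 1, under Consent, reports 1,267 intervention and 1,567 control participants. Its column headed "Participant range per cluster" shows 3-166 and 13-163, with means of 47 and 54.

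**The concern.** The section gives every quantity needed to check its own answer, and the answer comes out too small. The gap is about 400 to 760 participants per arm, more than a rounded figure can absorb.

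What is at stake is how the result will be read. A reader who accepts 80% power for a 25% reduction, and the plan's statement that no difference means failure, will take a null result as good evidence against the program. If the plan's inputs are right, a true 25% reduction would be missed about one time in three, not one in five.

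**Working it through.** **Inputs.** Control risk p1 = 0.168; 25% reduction; one-sided alpha 0.05 (z = 1.645); power 80% (z = 0.842); m = 50; ICC = 0.02; 1:1 allocation. So (1.645 + 0.842)² = 6.183. I take 16.8% as the cumulative event probability to age 20.

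The section does not say on which scale the 25% applies, so both readings are used:
- Risk ratio 0.75: p2 = 0.126, implied HR = ln(0.874)/ln(0.832) = 0.732.
- Hazard ratio 0.75: p2 = 1 − 0.832^0.75 = 0.1289.

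**What reproduces.** 6% + 10.8% = 16.8%. Design effect (DE) = 1 + (50 − 1) × 0.02 = 1.98, stated as 2.

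**What does not reproduce: 1,300 per arm.**

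- Two proportions: 6.183 × (0.168×0.832 + 0.126×0.874)/0.042² = 6.183 × 0.2499/0.001764 = 876 per arm before clustering.
- Schoenfeld, HR 0.732: events = 4 × 6.183/(ln 0.732)² = 255; divided by 0.168 + 0.126 = 0.294, this is 866 per arm.
- Schoenfeld, HR 0.75: events = 4 × 6.183/(ln 0.75)² = 299; divided by 0.2969 or 0.294, this is 1,007 to 1,016 per arm.
- Freedman, HR 0.75: events = 6.183 × (1.75/0.25)² = 303; divided by the same sums, this is 1,021 to 1,030 per arm.

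| Method | Per arm, DE 1 | Per arm, DE 1.98 to 2 | DE at which 1,300 suffices |
|---|---|---|---|
| Schoenfeld, HR 0.732 | 866 | 1,715-1,732 | 1.50 |
| Two proportions | 876 | 1,734-1,752 | 1.48 |
| Schoenfeld, HR 0.75 | 1,007-1,016 | 1,993-2,033 | 1.28-1.29 |
| Freedman, HR 0.75 | 1,021-1,030 | 2,021-2,061 | 1.26-1.27 |

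**Power at 1,300 per arm, one-sided, DE 1.98.**
- Two proportions: SE = √(1.98 × 0.2499/1300) = 0.01951; Φ(0.042/0.01951 − 1.645) = Φ(0.508) = 69%.
- Schoenfeld: effective events = 1300 × 0.294/1.98 = 193. HR 0.75: Φ(√193/2 × 0.2877 − 1.645) = Φ(0.354) = 64%. HR 0.732: Φ(√193/2 × 0.3117 − 1.645) = Φ(0.520) = 70%.
- With DE 2 the lowest of these falls to 63%.

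The reduction detectable with 80% power, by two proportions, solves 0.168r = 2.487 × SE(r). At r = 0.286, p2 = 0.120, SE = √(1.98 × 0.2453/1300) = 0.01933, and 2.487 × 0.01933/0.168 = 0.286. That is about 29%, not 25%.

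**Power for the recruited numbers (1,567 control, 1,267 intervention), equal school sizes, DE 1.98.**
- Two proportions: SE² = 1.98 × (0.1398/1567 + 0.1101/1267) = 0.000349, SE = 0.01867; Φ(0.604) = 73%.
- Schoenfeld: effective events = (1567×0.168 + 1267×0.126)/1.98 = 422.9/1.98 = 213.6; allocation factor 1567×1267/2834² = 0.2472. HR 0.75: Φ(√(213.6×0.2472) × 0.2877 − 1.645) = 67%. HR 0.732: 73%.

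**Unequal schools (secondary).** DE = 1 + ((1 + CV²)m − 1) × ICC. The article gives no standard deviation of school size. Assuming it is range/4, CV = (163/4)/47 = 0.87 and (150/4)/54 = 0.69, so DE is about 2.6. Replacing 1.98 by 2.6 above lowers power from 67-73% to about 57-63%. The direction is certain; the size rests on a guessed CV.

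**The case against.** **Clustering was called conservative and expected to decline.** This is the best defence. With the recruited numbers and 50 per school, two-proportion power reaches 80% at DE = (0.042/2.487)²/(0.1398/1567 + 0.1101/1267) = 1.62, an ICC of 0.62/49, about 0.013. By Schoenfeld with HR 0.75, DE must fall to about 1.40, an ICC of about 0.008. So the trial's true power is unknown, and the shortfall is conditional on ICC 0.02. The defence does not rescue the printed figure, though: the remark has no number, comes after the result, and sits beside a stated design effect of 2.

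**The article condenses a fuller calculation.** The cited method may use accrual and follow-up inputs that are not printed. Such inputs serve to obtain expected events, and the article already gives the cumulative pregnancy proportion. The inconsistency is between figures that are printed.

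**A milder gap.** About 1,500 per arm and 75% power result if 16.8% is applied to both arms together with an HR of 0.732. That HR already assumes 12.6% in the intervention arm, so the reading contradicts itself. Taking 16.8% as the intervention rate, with a continuity correction, gives 1,299 to 1,312, but the section says it is the control rate.

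**Recruitment.** A reader might infer that under-recruitment caused the problem, because 1,267 is below 1,300. It is 2.5% below an approximate target, and the total of 2,834 exceeds 2,600. At the same design effect, the recruited numbers give slightly more power than 1,300 per arm.

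**Consequence.** Recruitment ended in May 2006, and no planned estimate or test changes. This is fair: the correction concerns the stated figure and the reading of the result.

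**Conclusion.** The stated sample size is wrong on the plan's own inputs. They require about 1,715 to 2,060 per arm, and 1,300 gives about 63-70% one-sided power. The recruited numbers give about 67-73% with equal school sizes, and less with the sizes in Table 1. These figures assume ICC 0.02, a 16.8% cumulative control risk and a 25% reduction on either the risk or the hazard scale.

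Two stronger readings are tempting and are not supported:
- That the trial definitely lacks 80% power. The documents show only that the inputs and the stated number do not match; a lower ICC could restore the power.
- That the authors ran a two-sided calculation and left out the design effect. This matches numerically: with (1.960 + 0.842)² = 7.849, Schoenfeld at HR 0.75 gives 379 events, or 1,278 to 1,290 per arm. But it is an inference that nothing in the text confirms.

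Two-sided power, and power for births and abortions separately, do not bear on this point. The calculation was one-sided and for overall pregnancy.

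**What to change.** 1. Withdraw the statement that about 1,300 per arm gives 80% power for a 25% reduction.
2. State instead the power, or the reduction detectable with 80% power, for 1,267 and 1,567. Use the actual school sizes in DE = 1 + ((1 + CV²)m − 1) × ICC, and say whether the 25% is a risk or a hazard reduction.
3. Say that the figure is conditional on ICC 0.02. If a weaker clustering effect is to be relied on, give the ICC and the resulting power beside it.
4. Replace the reading of no difference as program failure with interpretation through the confidence interval: whether it excludes a 25% reduction.

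The cost is one recalculation, using school sizes the team already holds, and some rewording. No participants, data or analyses are added. The only downside is a less favourable stated power.

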**Methods and Design:**

Fifty-seven schools (86% of 66 eligible secondary schools) in Perth, Australia were recruited to the clustered (by school) randomised trial, with even randomisation to the intervention and control arms. Between 2003 and 2006, the VIP program was administered to 1,267 participants in the intervention schools, while 1,567 participants in the non-intervention schools received standard curriculum. Participants were all female and aged between 13-15 years upon recruitment. Pre and post-intervention questionnaires measured short-term impact and participants are now being followed through their teenage years via data linkage to hospital medical records, abortion clinics and education records. Participants who have a live birth are interviewed by face-to-face interview. Kaplan-Meier survival analysis and proportional hazards regression will test for differences in pregnancy, birth and abortion rates during the teenage years between the study arms.

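### The stated sample-size inputs do not give around 1,300 girls per arm: they require about 1,715 to 1,755, and 1,300 gives about 69–70% power, not 80%

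*Protocol article*

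**What the plan says.** The section on Sample Size Calculation in the protocol article lists its inputs and its result in one paragraph, after an average of 50 girls per school:

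- Clustering and effect: "a conservative intra class correlation (ICC) of 0.02 (equating to a design effect of 2), and sought to detect a 25% magnitude of difference".
- Error rates: "at the 5% significance level with 80% power". On sidedness: "Power calculations were made with a one sided test in mind".
- Control rate: "6% expected to have live birth, 10.8% abortion, and thus 16.8% known pregnancy".
- Result: "The minimum required number of participants was estimated to be around 1,300 per study arm".

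The paragraph names a published time-to-event method and makes no allowance for loss to follow-up. After stating the result, it adds that clustering was expected to weaken as the students left school, but gives no smaller ICC or design effect.

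On recruitment, the abstract reports that "the VIP program was administered to 1,267 participants in the intervention schools" and that 1,567 girls took part in the control schools. Table 1 gives the same counts.

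**The concern.** All the inputs needed to recompute the sample size are printed beside the result, so the result can be checked without any outside source. Doubling the usual unclustered size for these rates gives well over 1,300, so the text claims a power that its own inputs do not support.

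The interpretation of a null result is at stake. The same paragraph says that no difference, or an increase, would be taken as the program failing on its primary outcome. A reader would weigh that conclusion as coming from a trial with a 20% chance of missing a true 25% reduction. At the stated ICC that chance is about 30% at the planned size and about 27–28% at the recruited size. It is higher if the 25% is meant as a hazard ratio.

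**Working it through.** **Inputs** (all from Sample Size Calculation): control proportion 0.168; 25% reduction, so 0.168 × 0.75 = 0.126 and a difference of 0.042; one-sided α 0.05 (z = 1.645); power 0.80 (z = 0.842); 50 per school; ICC 0.02; equal arms; no loss to follow-up. Schools are taken as equal in size, which favours the document.

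**Design effect.** 1 + (50 − 1) × 0.02 = 1.98. The stated value of 2 is correct rounding, so the fault is not here.

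**Requirement, two proportions.**
- Variance sum: 0.168 × 0.832 + 0.126 × 0.874 = 0.2499.
- Unclustered: (1.645 + 0.842)² × 0.2499 / 0.042² ≈ 876 per arm (878 with pooled variance under the null).
- Clustered: 876 × 1.98 ≈ 1,734. With pooled variance and a design effect of exactly 2: 1,756.

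**Requirement, log-rank events (Schoenfeld).** This is the closer match to the planned survival analysis.
- Hazard ratio implied by the two proportions: ln(0.874)/ln(0.832) = 0.732.
- Events: 4 × (1.645 + 0.842)² / (ln 0.732)² ≈ 255.
- Unclustered: 255 / (0.168 + 0.126) ≈ 866 per arm. Clustered: 866 × 1.98 ≈ 1,715.

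**If the 25% is a hazard ratio of 0.75.** About 299 events, which is 1,007 to 1,018 per arm depending on how the intervention event rate is set. Clustered: about 1,990 to 2,035.

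**Attempt to reproduce 1,300.** No reading that keeps every stated input reaches it. It appears when an input is changed:

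| Change to the stated inputs | Per arm |
|---|---|
| Design effect 1.49 (ICC 0.01), proportions reading | 876 × 1.49 ≈ 1,305 |
| No design effect, two-sided test, hazard ratio 0.75 | about 1,293 |
| One-sided α of 0.10, design effect 2 | about 1,280 |

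The ICC 0.01 match also depends on the proportions reading. At hazard ratio 0.75, a design effect of 1.49 gives about 1,500.

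**Power at 1,300 per arm.** Standard error: √(1.98 × 0.2499 / 1,300) = 0.0195. Then 0.042 / 0.0195 = 2.153, and Φ(2.153 − 1.645) = 69.4%. The log-rank version at 0.732 gives 69.9%; at 0.75 it gives about 64%.

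**Power as recruited (1,267 intervention, 1,567 control).** Standard error: √{1.98 × (0.1101/1,267 + 0.1398/1,567)} = 0.0187. Then 0.042 / 0.0187 ≈ 2.249, and Φ(2.249 − 1.645) = 72.7%. Pooled variance gives 71.9%, the log-rank version at 0.732 gives 73.2%, and 0.75 gives about 67–68%.

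**Reduction detectable with 80% power** (proportions reading, design effect 1.98): about 28.6% at 1,300 per arm (16.8% to 12.0%) and about 27.5% as recruited (16.8% to 12.2%).

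**The case against.** The strongest defence is the sentence on declining clustering. It explains why the ICC of 0.02 is called conservative, and a modestly lower value restores the claim: as recruited, on the proportions reading, power reaches 80% at any design effect up to about 1.6 (ICC about 0.012 with 50 per school). That part stands. The shortfall belongs to ICC 0.02 and is not a fixed property of the trial. But the sentence supplies no lower value, and 0.02 is the only ICC printed, so it cannot make 1,300 the result of the listed inputs.

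It is also fair that the cited method's formula is not shown, and that planned power enters neither the Cox estimate nor its robust variance. The effect estimate, its interval and the type I error are untouched.

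Three stronger readings are tempting and should not be drawn:

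- *The calculation really used ICC 0.01.* This is one possibility. Other changed inputs also land near 1,300, and the document does not show which was used.
- *The intervention arm fell short of the minimum.* At 1,267 it is slightly under a figure given only as approximate, and the larger control arm more than offsets this: the balanced equivalent is 2/(1/1,267 + 1/1,567) ≈ 1,401 per arm.
- *More girls should have been enrolled.* The mismatch concerns a statement of power. It does not show what the true ICC is.

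**Conclusion.** Wrong as written. The printed inputs require about 1,715 to 1,755 per arm, at least 32% above 1,300 (1,715/1,300 = 1.32), or about 1,990 to 2,035 at a hazard ratio of 0.75. The word around cannot cover a gap of more than 400 girls per arm. At ICC 0.02 the stated 80% power is really about 69–70% at 1,300 per arm and about 72–73% as recruited (about 64% and 67–68% at hazard ratio 0.75).

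This rests on the document's own rates, a one-sided 5% test, equal schools of 50 and complete follow-up. A two-sided test makes the gap larger (about 2,200 per arm or more). The mismatch is established; its cause is not.

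**What to change.** Correct the sample-size paragraph in one of two ways.

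- If ICC 0.02 is the planning value, state that with 50 girls per school and a one-sided 5% test, 1,300 per arm gives about 69–70% power for a 25% reduction from 16.8%, and the recruited 1,267 and 1,567 give about 72–73%. Add that 80% power applies to a reduction of about 28.6% at the planned size and about 27.5% as recruited. Say whether the 25% is a difference in proportions or a hazard ratio; if the latter, give about 64% and 67–68%.
- If a different ICC or another input produced 1,300, state the value used and correct the listed input. If the expected decline in clustering was the reason, give the lower ICC that was assumed.

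The cost is a sentence or two and a less favourable power statement. No enrolment, endpoint, model or test changes.

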### Planned analyses for the Primary Outcome

#### Primary outcome - pregnancy

For live births, the birth date of the baby will be used as the outcome date. For abortions, the recorded admission date for abortion will be used. For overall pregnancies we will estimate the due date of a pregnancy for abortion cases by adding 6 months to the abortion date, as the majority of induced abortions take place in the first trimester. Where more than one pregnancy outcome is detected, the date of the first event will be used. Kaplan-Meier survival analyses will be undertaken for these primary outcomes. To adjust for clustering by school and potential confounding variables, the data will be analysed using Cox proportional hazards regression, using the Lin and Wei robust sandwich estimate of the variance-covariance matrix. All analyses will be undertaken using SAS or SPSS.

### Ethics Approval

Ethical approval to approach students to participate in the trial and to consent to be tracked via data linkage up to the age of 20 years was obtained from the Princess Margaret Hospital (PMH) Ethics Committee. Furthermore, ethics approval has also been granted by the Confidentiality of Health Information Committee which specifically reviews study applications requiring data obtained via the Western Australian Data Linkage System (WADLS).

### Project timetable

The study commenced in 2003 and is expected to be completed in late 2011 once all the participants reach 20 years of age.

## Discussion

The few available reports on Infant Simulator based pre-conception interventions are limited to attitudes and beliefs around teenage pregnancy and knowledge and self reported use of contraception. The results of these studies are contradictory and limited by small sample sizes and study design. While research indicates that cognitive measures are associated with behavioural measures among young people, evidence concerning associations between these measures and teenage pregnancy is inconclusive [7,44]. Furthermore, the validity of young people's expectations about sexual initiation and conception in predicting risk of teenage pregnancy has not been researched [7]. Despite this lack of evidence, it is estimated that more than 30,000 Australian students use the Infant Simulators annually [45] with greater numbers in the United States and Canada. It is imperative that the efficacy of Infant Simulator based programs is established and their costs and benefits documented. On the whole, randomised trials of theory based interventions have found minimal effect on teenage sexual behaviour or in reducing pregnancy [30,32,46]. The need for better research designs, long-term follow-up and the assessment of pregnancy outcomes has been acknowledged by others evaluating Infant Simulator based programs [21-24,28].

This trial presents the first and only long term follow-up of pregnancy outcomes to evaluate an Infant Simulator based program. The authors are aware of only one other long term evaluation of an Infant Simulator based teen pregnancy prevention program where pregnancy outcomes have been tracked. While Hillman's thesis concluded that the BTIO intervention had been successful in delaying pregnancy by up to a year among its participants compared to a control group during a follow-up period of 3-5 years, her conclusions were based on a limited sample size of 221 students [47]. In addition Hillman was not able to track induced abortion as well as live birth outcomes such as this study.

In addition to this study being the first of its kind, it also has high generalisability (external validity) due to the wide coverage in public and (non catholic) private schools across the entire Perth metropolitan area providing variation in social and economic circumstances. The program has also been delivered by School Health Nurses, existing staff within the school, and participation by students was non-compulsory. Although this self-selection potentially creates participation bias for the Trial, it also represents the usual choice that is occurring for participation in such programs in schools. Furthermore, the VIP Program content has been developed according to best practice in health promotion delivery, and refined over a number of years. Results will therefore represent the impact of an Infant Simulator based program with optimal delivery. Internal validity of the study has been maximised by the use of uniform training of the School Health Nurses, utilisation of a Training Manual clearly outlining the process, and by pre-specified programming of the Infant Simulators in each of the schools. Furthermore, the scope of the data collected is comprehensive and the quality of data is high. It is estimated that the study will achieve over 95% coverage of live birth and induced abortion outcomes in the State via data linkage and direct approach to abortion clinics (2009, unpublished data, WA Department of Health). While it is not possible to determine the number of cases lost to follow-up on the primary outcome, average migration rates from the state on an annual basis are low, less that 0.5% of the population [48].

The main limitation to this Trial is the potential bias associated with low participation rates. The participation rates achieved by this Trial occurs in the broader context of declining participation rates in epidemiological studies over the past thirty years [49]. Barriers to participation in this study included requiring active consent of both the parent and participant; the sensitive nature of the Program content (i.e. sex education); and the request for identified access to sensitive data (birth and abortion) via linkage to medical records. Furthermore, randomisation occurred at the cluster level and not at the individual level and each student knew prior to participation in the Trail if they were going to care for an Infant Simulator or not. Indeed, it was easier to recruit participants for the intervention arm with caring for the Infant Simulator acting as an incentive in itself, with a participation rate of 58% compared to 45% in the control arm, where there was no obvious benefit to the student's participation. The higher participation rate in the case group is consistent with other population case-control studies [50] and specifically in adolescent pregnancy prevention studies. Aarons reported consent rates among 7^th ^and 8^th ^graders in US schools from 78-80% in the intervention group and 67-72% in the control group [51]. Elsewhere, others have reported that when active parental consent is sought, parental consent is typically obtained for 30-60% of students [52]. Only two of the BTIO evaluation papers reported rates of parental consent and these were 57% of US 8^th ^graders (13-15 years old) [20] and 60% of US 10^th ^or 12th graders (16-18 years old) [53]. Seeking approval for linkage to sensitive medical records further contributes to the relatively low rates. One Australian study reviewed participation rates for linking survey data to health service records and found that the lowest consent rates were amongst young women of whom only 37% initially agreed (Young et al, 2001).

Recruitment bias becomes a threat to the external validity if there are systematic differences in the characteristics of participants in the intervention and control arms that are associated with the exposure or outcome variables. Unfortunately, the study was unable to collect information from the students who did not participate or the parents who failed to provide consent. Therefore we can only anticipate differences between participants and non-participants based on the best available evidence. In general epidemiological studies, participants are more likely to be of higher socioeconomic status, employed, married and of better health status. Further, in studies of risk behaviours, those engaged in those behaviours are less likely to participate [49] The requirement for active parental consent has been associated with the lesser representation of ethnic minorities, students having problems at school and students already engaged in or at risk of problem behaviours [52,54]. So while the study cannot control for systematic differences between participants and non-participants, it can statistically control for potential baseline differences between the intervention and control groups. The following data has been collected by the Trial to investigate and control for potential confounders: socio-economic status, family type, whether the participant had ever had sexual intercourse, had ever had responsibility for caring for a baby, reported importance and intention of going to University or further education, level of psychological distress, and smoking, drug and alcohol use. These variables were measured at the time of entry into the Trial. Additionally each participant's educational attainment data has been linked to the Trial data to enable controlling for academic success.

In conclusion although the pragmatic nature of the trial and the low participation rates will provide some complexities for the analyses, the results will have international significance and advance the evidence to inform school based teen pregnancy prevention programs.

